**Fig. 1 Fig1:**
[figure not shown]
Study design. Study design of the POSITIVE study (Part III)

All potential study participants at the Clinic for Thoracic Diseases Heidelberg are screened for eligibility during tumor board sessions by physicians and study personnel. Eligible patients are contacted by the study physicians; patients who provide written informed consent are scheduled for baseline assessment (T0). Randomization (block randomization, 1:1 ratio, random block sizes) to the study arms is carried out on the basis of prepared randomization lists stratified by primary treatment with radiotherapy (yes/no), histology (NSCLC/SCLC), the presence of brain metastases (yes/no) and sex (male/female).

### Objectives

Primary endpoints are (1) quality of life as measured by the FACT-L questionnaire, subcategory Physical Well-Being and (2) general fatigue measured by the Multidimensional Fatigue Inventory (MFI-20). As secondary endpoints, we evaluate whether the intervention has a positive impact on physical performance, depression, anxiety, demoralization and immunological parameters. In addition, sustainability and long-term effects of the intervention will be analyzed during the follow-up period.

### Interventions

For patients with advanced lung cancer the adequate management of disease- and treatment-related side effects determines quality of life, psychosocial burden and the extent of fatigue. Therefore weekly phone calls are provided to all patients. Care management phone calls (CMPC) are based on the Edmonton Symptom Assessment Scale (ESAS), a 9-item patient-rated symptom visual analogue scale developed for patients receiving palliative care. The modified version is comprised of one additional question to assess the patients’ quality of life. Patients rate their symptoms on an 11-point scale from 0 to 10 and at pre-specified cut off values (e.g. uncontrolled pain or breathlessness) the attending physician is contacted by the study nurse to manage symptoms and side-effects.

The exercise intervention program (EIP) contains resistance and endurance training in supervised and non-supervised sessions. Supervised training sessions are performed during patients’ inpatient stay at the clinic or in the outpatient setting near patients’ hometown in cooperating training centers within a regional network called ‘OnkoAktiv’. Non-supervised training sessions are conducted home-based. For that purpose patients receive an exercise manual and are instructed by a physiotherapist or sports scientist in individualized home-based exercises.

Exercise training is scheduled 3 times a week. The intensity of the endurance training sessions is 70-85 % of estimated maximum heart rate. Depending on patients’ individual endurance capacity, training starts at a duration of at least 15 min with subsequent increases to 45 min. Training duration and intensity for the home-based sessions is tailored using the RPE (Rate of Perceived Exertion) scale (Borg) and a well-established self-rating procedure from our lung cancer feasibility and allogeneic transplant study [44, 45]. Specifically, at the beginning of each training session patients are asked to complete an assessment of pain, fatigue, emotional status, and distress. This assessment is used to self-rate patients’ well-being and group them into 3 different categories, represented by the traffic light colors red, yellow and green, for tailoring the exercise intervention. Depending on subjectively rated well-being, the patient performs higher or lower intensity training. After each training session patients are asked to document their training in a training log. The supervised training sessions in the local outpatient training center include resistance exercise on machines and endurance training on an ergometer/treadmill. In the outpatient setting, patients and exercise specialists in cooperating training centers are instructed accordingly. During the first 12 weeks of the intervention program, supervised training sessions are conducted twice a week with an additional self-administered home-based training once a week. With the beginning of week 13 supervised training in cooperation training centers is reduced to 1x/week and patients are instructed to perform two home-based training sessions per week.

Supervised resistance and endurance training protocols comply with the American College of Sports Medicine (ACSM) exercise guidelines for cancer survivors [46] and with ACSM recommendations for progressive resistance training for novice weightlifters and older adults for one to three sets at a weight that can be done/lifted for 8 to 12 repetitions (approximately 60–80 % of 1-RM) [47, 48].

On the basis of the CMPCs the study nurse regularly reviews exercise adherence and identifies barriers and problems with regard to exercise. Exercise sessions are temporarily interrupted if pain, dizziness, or other contraindications (infections with body temperature ≥38 °C, impaired hematopoietic capacity) occur.

### Diagnostic procedures

All diagnostic procedures used in the POSITIVE study (Part III) are summarized in Table 2.

**Table 2 Tab2:** Diagnostic outcomes. Assessments and instruments used in the POSITIVE study (Part III)

Outcomes	Instrument	T0	T1	T2	T3	T4
Primary endpoints						
• Physical well being	Functional Assessment for Cancer Therapy – Lung	x	x	x	x	x
• General fatigue	Multidimensional Fatigue Inventory	x	x	x	x	x
Secondary endpoints						
• Physical performance (muscle strength and endurance capacity)	Spirometry, Six-Minute Walk Test, hand-held dynamometry, exercise log	x	x	x	x	x
• Psychosocial parameters (depression, anxiety, demoralization)	Ultra-Brief Patient Health Questionnaire (PHQ-4), Demoralization Scale, locus of control, Mini Nutrition Assessment	x	x	x	x	x
• Immunological parameters (cellular immunity, cytokine and chemokine panels in T-lymphocyte subsets)	Quantification of immune cell populations and tumor antigen reactive effector (memory T cells), detection of tumor reactive regulatory T cells, quantification of key immune effector molecules in serum.	x	x	x		
Others						
• Care management phone calls	Edmonton Symptom Assessment Scale	weekly				

*Abbreviations*: T0: Baseline; T1: 12 weeks after randomization; T2: 24 weeks after randomization; T3: 1st follow-up at week 40 after randomization; T4: 2nd follow-up at week 52 after randomization

## Questionnaires

Validated questionnaires are used to assess emotional and physical well-being and to assess study outcomes.

To evaluate the primary objective “quality of life” in the subcategory “physical well-being” the lung specific part of the Functional assessment of Cancer Therapy-Lung (FACT-L) [49] is used. FACT-L is widely used in clinical studies and has already been applied in exercise intervention studies in lung cancer patients [50–52]. The PHQ-4 questionnaire is a short instrument to detect the extent of depression and anxiety [53], providing sufficient diagnostic accuracy for major depression. To evaluate the extent of chronic fatigue the Multidimensional Fatigue Inventory (MFI) is used. The MFI is divided into the five subscales “general fatigue”, “physical fatigue”, “mental fatigue”, “reduced motivation” and “reduced activity” [54] and is a proven tool in numerous oncological studies [55–57]. The Demoralization Scale (DS) [58] reliably detects the extent of existential distress in cancer patients [59] and describes the individual incapacity to cope effectively with stressful situations. The locus of control questionnaire [60, 61] measures the self-efficacy in terms of illness and health and was adapted to oncological patients to analyze perceptions of control in cancer patients [61].

The nutritional status of the patients is assessed with the Mini Nutritional Assessment (MNA). The screening part of the questionnaire allows the detection of malnutrition [62].

## Pulmonary function tests

Pulmonary function tests (PFT) are conducted to assess vital capacity (VC) and Forced Expiratory Pressure in one second (FEV1). These tests are performed during staging appointment at the Clinic for Thoracic Diseases Heidelberg.

## Physical function tests

Functional capacity is assessed by the 6-min walk test (6MWT). The 6MWT [63] is a feasible and safe test to determine patients physical functioning and is well established in cancer patients [64]. Patients are instructed to walk over a pre-measured distance of 30 m in six minutes (6-min walk distance, 6MWD) as many meters as possible. Oxygen saturation and pulse rate are monitored concomitantly before, during and after testing. After the test, patients are asked to rate their individual perceived exertion using the Borg Scale [44].

The hand-held dynamometry measures maximal voluntary isometric contraction in Newton meters in various muscle groups (device from CITEC©, Netherlands). It is a valid and reliable instrument to measure muscular strength [65]. In this study, for each test session six major muscle groups including upper and lower extremities (knee and elbow flexors and extensors, hip flexors and abductors) are assessed bilaterally for their isometric power. For each muscle group the patient performs three sets of which the best value is used in the analysis.

## Exercise log

After each training session patients randomized to the exercise training group are asked to complete an exercise log according to the FITT (Frequency, Intensity, Time and Type of exercise) criteria. Furthermore, patients are asked to report mood expressions prior and after the training sessions as well as problems or symptoms with regard to the exercise program. The perceived exertion of each exercise session is rated with the Borg Scale [44].

### Translational Program

For biomarkers of immune function EDTA blood and serum is collected and processed by the Immune Monitoring Unit at the German Center Research Center (DKFZ) Heidelberg and used to generate mononuclear cells (PBMC, cryopreserved until analysis). Using flow cytometry the question will be addressed whether exercise skews the immune response towards a pro-inflammatory phenotype by reducing the regulatory T cell frequencies. Quantification of tumor antigen reactive effector T cells will be done by IFN-γ Elispot assays from cryopreserved peripheral blood monocytes (PBMC) using a panel of defined tumor-associated antigens (TAA). These include MUC1, Her-2/neu, EGFR, telomerase and survivin [66]. Key immune effector cytokines and chemokines will be quantified through luminex technology from cryopreserved serum samples.

### Sample size

Power calculations were based on statistical tests for the group effect in the analysis of covariance for the two endpoints FACT-L-PWB and MFI tested in step 1 of the multiple testing strategy (see section Statistical Analysis). The total planned sample size is *N* = 250 (125 per arm). Patients dropping out before week 24 are not replaced. Assuming an accrual rate of about 8 patients per month the projected accrual time is approximately 2.5 years.

Power calculations were done using computer simulations written in R code. We assumed normally distributed variables with identical standard deviations at T0 and T1 weeks and an identical exponential correlation structure in both groups. Standard deviations and correlations were estimated from the pilot study. With *n* = 75 evaluable patients per group the power to detect an effect size (e) of 0.4 is 72.0 % and 80.9 % for MFI and PWB (resp.); for e = 0.45 the power is >80 % for each end point separately (5000 simulation runs per scenario). This implies that for an effect size of e ≥ 0.4 - corresponding to an estimated absolute difference (between the mean values measured at T0 and T1) of 1.35 in case of MFI and 1.6 for the PWB -, the power to detect at least one true effect if both alternative hypotheses are true is >80 %. A sample size of ≥75 evaluable patients per group corresponds to a drop-out rate of ≤ 40 %, which appears realistic. Thus, assuming an estimated 1-year survival rate of 40 % and survival times following an exponential distribution (resulting in a median survival of about 9 months), the 12-week death rate is 19.1 %.

### Data analysis

The statistical analysis of the primary and secondary quality of life (QoL) endpoints will be based on all randomized patients for whom T0 and T1 measurement are available. The main analysis of the primary and secondary QoL endpoints will use an analysis of covariance with the following regression equation:$$ \mathbf{Q}\left(\mathbf{T}\mathbf{1}\right) = \mathbf{constant} + \mathbf{a} \times \mathbf{Q}\left(\mathbf{T}\mathbf{0}\right) + \mathbf{b} \times \mathbf{intervention}\ \mathbf{group}, $$where Q(t) denotes the value of the QoL endpoint measured at timepoint t. The statistical testing for the group effect will be done for each primary endpoint separately. The multiple test procedure will be as follows: in a first step, the group effect for FACT-L PWB and MFI will be tested using a Bonferroni adjustment (i.e. at nominal α = 2.5 %). In a second step, FACT-L PWB and FACT-L Total will be tested using a hierarchical ordering of the hypotheses; i.e., the test regarding FACT-L Total will only be performed (again at the α = 2.5 % level) if the test for FACT-L PWB yields a significant result at the 2.5 % level. This testing strategy comprising three hypotheses controls the multiple (family-wise) level of significance α = 5 %. It is anticipated that quality of life and physical performance data will be available for most patients who are alive at week 12.

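### The main ANCOVA omits the four factors used to stratify randomisation; adding them is a free but minor efficiency gain

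*Protocol article*

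**What the plan says.** The randomisation paragraph of the Study design section describes 1:1 allocation ("block randomization, 1:1 ratio, random block sizes") from lists "stratified by primary treatment with radiotherapy (yes/no), histology (NSCLC/SCLC), the presence of brain metastases (yes/no) and sex (male/female". Four binary factors make 16 strata. No reason is given for choosing these four.

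The Data analysis section introduces the model with "The main analysis of the primary and secondary QoL endpoints will use an analysis of covariance with the following regression equation". Written out, it is Q(T1) = constant + a × Q(T0) + b × intervention group. No stratification factor appears there, and no other section adds one. In the first step of the testing strategy, FACT-L PWB and MFI "will be tested using a Bonferroni adjustment (i.e. at nominal α = 2.5" per cent each. Only patients with both a T0 and a T1 measurement are analysed.

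The Sample size section bases power on the group effect in this ANCOVA. With 75 evaluable patients per group, "the power to detect an effect size (e) of 0.4 is 72.0 % and 80.9 % for MFI and PWB (resp"; at an effect size of 0.45, "the power is >80 % for each end point separately (5000 simulation runs per scenario".

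**The concern.** Stratified allocation restricts how far the arms can differ on the four factors. If a factor predicts the outcome and is left out of the model, its variance stays in the residual, although much of its contribution to the sampling error of the arm difference has been designed away. The model-based standard error then overstates the real variability of b: confidence intervals are a little too wide and the test falls below its nominal level.

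What is at stake is precision. It matters most for MFI, whose stated power at e = 0.4 is below 80%. Because the article prints the regression in full, this is a stated model choice and not a detail left to the analysis plan.

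**Working it through.** **Inputs from the protocol.** 75 evaluable of 125 per arm, so 60% retained; α = 0.025 per primary endpoint; e = 0.4; power 72.0% (MFI) and 80.9% (PWB). The implied SDs are 1.35/0.4 = 3.375 (MFI) and 1.6/0.4 = 4.0 (PWB); the calculation below is in SD units.

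**Assumptions.** The test is two-sided (sidedness is not stated). The T0–T1 correlation ρ is not printed and is solved from the stated power. R², the share of residual variance after Q(T0) that the four factors explain, is not in the documents and is shown as a range. Loss is random.

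**Step 1: the plan's own figures.** SE = √[(1 − ρ²) × 2/75]; the critical t on 147 df is 2.265.

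- MFI: ρ = 0.510 gives SE = 0.860 × 0.1633 = 0.1404, noncentrality 0.4/0.1404 = 2.849, power 72.0%.
- PWB: ρ = 0.626 gives SE = 0.7795 × 0.1633 = 0.1273, noncentrality 3.142, power 80.9%.
- At e = 0.45 the same correlations give 82.5% and 89.7%, in line with the stated figure of more than 80% for each.

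Since ρ was back-solved, this shows consistency and is not an independent reproduction. It does show that the stated powers fit the model without stratification terms.

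**Step 2: power with the four main effects.** Residual variance is multiplied by (1 − R²), and df fall from 147 to 143.

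| R² | MFI | PWB |
|---|---|---|
| 0 | 72.0% | 80.9% |
| 0.02 | 72.9% | 81.7% |
| 0.05 | 74.4% | 83.0% |
| 0.10 | 76.9% | 85.1% |

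**Step 3: the unadjusted test under stratification and 40% loss.** The comparator is not simply 72.0% and 80.9%, because stratification also helps the unadjusted estimate. With perfect balance at randomisation and 60% retained at random, about 40% of the imbalance variance of simple randomisation returns. Relative to the variance the model assumes, the true variance is (1 − R²) + 0.4R² = 1 − 0.6R². Write k = √(1 − 0.6R²). The SE is too wide by 1/k, the level is 2 × P(t₁₄₇ > 2.265/k), and power is about Φ[(noncentrality − 2.265)/k].

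| R² | k | SE excess | True level | MFI power | PWB power |
|---|---|---|---|---|---|
| 0.05 | 0.985 | 1.5% | 2.3% | 72.3% | 81.4% |
| 0.10 | 0.970 | 3.1% | 2.1% | 72.6% | 81.7% |

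Subtracting from Step 2, the gain is about 2.1 (MFI) and 1.6 (PWB) points at R² = 0.05, and about 4.3 and 3.4 at R² = 0.10. This is slightly generous, because it ignores the cost of correcting the imbalance left after loss.

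**Step 4: simulation.** 250 patients were randomised in stratified blocks, with 75 per arm evaluable after random loss and assumed factor prevalences of 40/20/20/40%. In 8,000 runs the gains were about 1.8 (MFI) and 1.6 (PWB) points at R² = 0.05, and 3.5 and 3.0 at R² = 0.10. A second simulation with 40% random loss and 5,000 runs gave 71.3% against 73.2% (MFI) and 81.5% against 82.3% (PWB) at 0.05, and 72.0% against 76.1% and 80.9% against 84.0% at 0.10. Each simulated power carries a Monte Carlo SE of about 0.5 point (√(0.82 × 0.18/5000)), so the 0.8-point PWB gain is compatible with the rest. The unadjusted level was about 2.2% at both values of R². At R² = 0 there was no gain; the cost of the extra terms was under 0.1 point analytically and 0.4–0.8 point in simulation.

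**The case against.** The case against has real force on size and certainty.

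- **Validity is untouched.** The power calculation and the analysis use the same model, so design and analysis agree. What is forgone is power the plan never claimed. This stands.
- **The loss is conditional.** A reader might infer that the factors were chosen as prognostic. The protocol does not say so, and if they explain nothing beyond Q(T0) the loss is nil. This stands.
- **The level is easily exaggerated.** A reader might compute 2 × [1 − Φ(2.265/√(1 − R²))] and report a level of 2.0% to 1.7% at R² of 5–10%. That assumes near-perfect balance among those analysed, against a planned loss of up to 40%. It also puts a t critical value into a normal formula, which returns 2.35% even at R² = 0. The documents do not support it.
- **The gain is easily exaggerated.** Setting 76.9% against 72.0% suggests 4.9 points for MFI, but ignores what stratification already does for the unadjusted test.
- **The design target does not depend on it.** The Sample size section aims for more than 80% power to detect at least one true effect at e ≥ 0.4, which PWB alone meets at 80.9%.
- **Supportive adjusted analyses may exist in an unseen plan.** That is possible, but it would not alter the main model as printed.

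None of this removes the mismatch between how patients are randomised and how they are analysed, or makes the remedy costly.

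**Conclusion.** The point holds as a free improvement with a minor efficiency gain. Under R² of 5–10% and 40% random loss, adjustment adds about 1.5–2 to 3–4 points of power, the unadjusted SE is about 1.5–3% too wide, and the test runs at roughly 2.1–2.3% instead of 2.5%. These figures also rest on two-sided testing, back-solved correlations and, for the simulations, assumed factor prevalences.

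A reader might go further and infer that the primary result would be biased, that type I error is inflated, or that the stated 72.0% and 80.9% are too high. None of these follows: the omission leaves the estimate unbiased, makes the test conservative, and is already reflected in the stated powers.

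**What to change.** Pre-specify, before any unblinded analysis:

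Q(T1) = constant + a × Q(T0) + b × group + c₁ × radiotherapy + c₂ × histology + c₃ × brain metastases + c₄ × sex

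Apply it to the two primary endpoints and the other quality-of-life endpoints covered by the Data analysis section, including FACT-L Total. Main effects suffice; terms for all 16 strata are not needed. State that the histology term is dropped if no SCLC patients are enrolled: Table 1 lists only NSCLC, while the Study design text and the strata include SCLC.

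The cost is one line of text and 4 of 147 residual degrees of freedom. No new data are needed, since the factors are already recorded for randomisation.

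### The testing rule passes alpha only from PWB to FACT-L Total; passing it between the PWB/Total and MFI branches as well would add power at the same 5% family-wise level

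*Protocol article*

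**What the plan says.** The Data analysis section sets out a complete rule for three hypotheses. First, "in a first step, the group effect for FACT-L PWB and MFI will be tested using a Bonferroni adjustment", each at a nominal 2.5%. Then, "In a second step, FACT-L PWB and FACT-L Total will be tested using a hierarchical ordering of the hypotheses": FACT-L Total is tested, again at 2.5%, only "if the test for FACT-L PWB yields a significant result" at that level. The section concludes: "This testing strategy comprising three hypotheses controls the multiple (family-wise) level of significance" at 5%. It does not say whether tests are one- or two-sided; it says only that "The statistical testing for the group effect will be done for each primary endpoint separately".

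The Sample size section states that, with 75 evaluable patients per group, "the power to detect an effect size (e) of 0.4 is" 72.0% for MFI and 80.9% for PWB, and that at e = 0.45 each endpoint separately exceeds 80%. Its design criterion is that "the power to detect at least one true effect if both alternative hypotheses are true is" above 80%.

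**The concern.** Alpha moves along one path only, from PWB to FACT-L Total. Two other paths are left closed:

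- If MFI is significant, its 2.5% is spent. PWB is still judged at 2.5%, and so is FACT-L Total.
- If PWB and FACT-L Total are both significant, their 2.5% is spent. MFI is still judged at 2.5%.

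In either case the 5% allowance is not fully used. Opening these paths costs no patients and no error control. What is at stake is power for each primary endpoint, for both together and for FACT-L Total. The Discussion expects improvement in both quality of life and fatigue at 12 weeks, so success on both is of interest to the trial even though it is not the sample-size criterion.

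**Working it through.** **1. The plan's own error claim.** The two branches have levels 0.025 + 0.025 = 0.05. PWB followed by FACT-L Total is a fixed sequence inside the PWB share, so the bound covers all three hypotheses. The stated 5% is reproduced.

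**2. The plan's own powers.** The 72.0% and 80.9% cannot be rebuilt independently, because "Standard deviations and correlations were estimated from the pilot study" and those values are not given. They are plausible. For an analysis of covariance with residual SD √(1 − ρ²), 75 per group and e = 0.4 at two-sided 2.5%, they correspond to baseline-to-week-12 correlations of 0.50 (MFI) and 0.62 (PWB). The same correlations give 82.5% and 89.7% at e = 0.45, which agrees with the stated figure of over 80%. At two-sided 5% they give 80.6% (MFI) and 87.6% (PWB) at e = 0.4.

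**3. The alternative.** Start with PWB 2.5%, MFI 2.5%, Total 0. Transitions, each with weight 1: PWB→Total, Total→MFI, MFI→PWB.

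- Nothing is lost: PWB and MFI are each still tested at no less than 2.5%, and so is Total once PWB is significant at 2.5%. In simulation the loop kept every rejection made by the planned rule.
- Error control: the levels in use never sum to more than 5%. Seven null configurations were simulated with independent statistics, and the loop's family-wise error was at most 5.0% within simulation error. With MFI strongly effective and PWB and Total null, the planned rule uses 2.5% and the loop 5.0%. With only MFI null, or only Total null, the figures are again 2.5% and 5.0%.
- At least one primary: Total starts with no alpha, so the first rejection must be PWB or MFI at 2.5%. This probability is therefore the same under both rules.

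**4. Size by hand, independent statistics, Total effect equal to PWB's.**

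- PWB: 0.809 + 0.720 × (0.876 − 0.809) = 0.857
- MFI: 0.720 + 0.809 × 0.809 × (0.806 − 0.720) = 0.776
- Both, planned: 0.809 × 0.720 = 0.582
- Both, loop: 0.582 + 0.720 × 0.067 + 0.809 × 0.809 × 0.086 = 0.687

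**5. Size by simulation.** Each row uses 2,000,000 trivariate normal draws, two-sided, calibrated to 80.9% and 72.0% at 2.5%. The documents do not give the correlations or the FACT-L Total effect, so both are assumed. Total's stand-alone power at 2.5% is set to 50% or 80.9%. On the z scale that is a mean of 2.241 or 3.116, and 2.241/3.116 = 72% of PWB's effect. Correlations are in the order PWB-MFI, PWB-Total, MFI-Total. All results are percentages; arrows run from the planned rule to the loop.

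| Correlations | Total alone | PWB, loop | MFI, loop | Total | Both primaries | At least one, either rule |
|---|---|---|---|---|---|---|
| 0, 0, 0 | 50 | 85.8 | 75.5 | 40.5 → 49.9 | 58.3 → 66.6 | 94.7 |
| 0, 0, 0 | 80.9 | 85.8 | 77.7 | 65.5 → 73.6 | 58.3 → 68.8 | 94.6 |
| 0.3, 0.5, 0.3 | 50 | 85.0 | 75.1 | 45.9 → 54.4 | 61.2 → 68.4 | 91.7 |
| 0.3, 0.5, 0.3 | 80.9 | 85.0 | 77.3 | 70.0 → 76.3 | 61.2 → 70.7 | 91.7 |
| 0.5, 0.7, 0.5 | 50 | 84.5 | 74.7 | 48.1 → 56.4 | 63.6 → 69.8 | 89.4 |
| 0.5, 0.7, 0.5 | 80.9 | 84.5 | 77.2 | 72.5 → 77.7 | 63.5 → 72.3 | 89.4 |
| 0.7, 0.8, 0.7 | 50 | 83.8 | 74.0 | 49.1 → 57.6 | 66.2 → 71.1 | 86.6 |
| 0.7, 0.8, 0.7 | 80.9 | 83.8 | 76.9 | 74.0 → 78.3 | 66.2 → 74.1 | 86.7 |

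**6. Why this particular loop.** A Holm step on PWB and MFI, with Total tested only after both, is not uniformly better than the plan. In the same scenarios it loses Total rejections that the planned rule makes in 1.7% to 12.7% of draws.

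**The case against.** The strongest reply is that nothing here is wrong. The rule is prespecified, unambiguous and simple, and its error claim is true. The sample size rests on detecting at least one effect, and no recycling scheme can change that probability. The 72.0% for MFI belongs to e = 0.4; at e = 0.45 the plan reports more than 80% for each endpoint. The size of the gain depends on inputs the article does not give, and MFI's gain can shrink to about 2 points because it requires FACT-L Total to be significant too. Enrolment began in November 2013, so this would change a confirmatory rule in a running trial.

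All of that stands, and it makes this an efficiency gain rather than the repair of an error. It does not remove the point. The direction of the gain does not depend on the assumptions, and the planned rule never rejects anything that the loop would not.

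A reader might infer from the word Bonferroni that no alpha is passed on at all. The documents do not support that, because the next sentence carries PWB's 2.5% to FACT-L Total. Nor do they support reading this as a failure of family-wise control or as a reason to change N. That FACT-L Total is not named as an endpoint in Objectives or Table 2 is a separate reporting matter and says nothing about the rule.

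**Conclusion.** The point holds as a worthwhile, inexpensive improvement to a valid plan. No alpha moves between the MFI branch and the PWB/FACT-L Total branch, and the loop dominates the planned rule at the same 5%. Over the assumed range, PWB power rises from 80.9% to about 84-86%, MFI from 72.0% to about 74-78%, both primaries from 58-66% to 67-74%, and FACT-L Total from 40-74% to 50-78%. The dominance is weak: power for at least one primary endpoint (about 87-95% in these scenarios) is identical, so the sample-size argument is untouched.

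The existence of the gain is certain. Its size rests on two-sided tests, the assumed correlations, the assumed FACT-L Total effect and the plan's own powers at e = 0.4.

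**What to change.** Keep the initial split and add two sentences to Data analysis:

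- If MFI is significant at 2.5%, PWB is tested at 5% and, if that is significant, FACT-L Total is tested at 5%.
- If PWB and FACT-L Total are both significant at 2.5%, MFI is tested at 5%.

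State the initial levels (PWB 2.5%, MFI 2.5%, Total 0) and the three transitions so that the loop cannot be read as a Holm step with FACT-L Total last. Settle and date the change before any comparative outcome data are seen. The article describes no blinding, so a reference to unblinding would not fix the time.

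The cost is a short amendment, with no new data and no extra patients. The one statistical drawback is that simultaneous confidence intervals matching the loop are less simple than Bonferroni intervals.
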